## Abstract

**Background:**

Critically ill patients are at increased risk of health care-associated infections due to various devices (central line-associated bloodstream infection, catheter-associated urinary tract infection, and ventilator-associated pneumonia), which pose a significant threat to this population. Among several strategies, daily bathing with chlorhexidine digluconate, a water-soluble antiseptic, has been studied as an intervention to decrease the incidence of health care-associated infections in the intensive care unit; however, its ability to reduce all health care-associated infections due to various devices is unclear. We designed the Daily Chlorhexidine Bath for Health Care Associated Infection Prevention (CLEAN-IT) trial to assess whether daily chlorhexidine digluconate bathing reduces the incidence of health care-associated infections in critically ill patients compared with soap and water bathing.

**Methods:**

The CLEAN-IT trial is a multicenter, open-label, cluster randomized crossover clinical trial. All adult patients admitted to the participating intensive care units will be included in the trial. Each cluster (intensive care unit) will be randomized to perform either initial chlorhexidine digluconate bathing or soap and water bathing with crossover for a period of 3 to 6 months, depending on the time of each center’s entrance to the study, with a 1-month washout period between chlorhexidine digluconate bathing and soap and water bathing transitions. The primary outcome is the incidence of health care-associated infections due to devices. The secondary outcomes are the incidence of each specific health care-associated infection, rates of microbiological cultures positive for multidrug-resistant pathogens, antibiotic use, intensive care unit and hospital length of stay, and intensive care unit and hospital mortality.

**Conclusion:**

The CLEAN-IT trial will be used to study feasible and affordable interventions that might reduce the health care-associated infection burden in critically ill patients.

## INTRODUCTION

Health care-associated infections (HCAIs) are common preventable illnesses in hospitalized critically ill patients^(
1
)^ and are associated with increased health care costs, length of stay, and mortality.^(
2
-
5
)^ Critically ill patients are at increased risk for HCAIs due to a myriad of factors, such as the use of invasive devices (endotracheal tubes, central lines, and urinary catheters) and their underlying critical illness. Practices such as care, device insertion bundles, and hand hygiene are the cornerstones of infection prevention^(
6
-
9
)^ and a major focus of infection and prevention control services, with several clinical trials evaluating infection prevention strategies in the critical care setting.^(
10
-
15
)^

Chlorhexidine digluconate (CHG) is a water-soluble, low-foaming, topical antiseptic agent included on the list of essential medicines of the World Health Organization;^(
16
)^ CHG exhibits activity against gram-positive and gram-negative bacteria, yeasts, and lipophilic viruses with a possible benefit of residual antibacterial activity.^(
17
)^ Chlorhexidine digluconate has been used in impregnated vascular catheter dressings, skin preparation for invasive procedures, preoperative bathing, and oral decontamination.^(
18
-
20
)^

The use of daily bathing with CHG to reduce HCAIs in critically ill patients has been evaluated in several studies, with mixed results indicating that it decreases the risk of some infections (central line-associated bloodstream infection [CLABSI] and bacteremia) while increasing the risk of others (ventilator-associated pneumonia [VAP]).^(
14
,
15
,
21
,
22
)^ The role of CHG bathing in reducing HCAIs has not been properly evaluated in low- and middle-income countries (LMICs), where the incidence and burden of HCAIs are greater.^(
1
,
23
,
24
)^ A cluster randomized design is desirable when studying interventions to reduce HCAIs given the possible benefit of the spillover effect and the reduction of contamination between the treatment and control groups.^(
25
,
26
)^

The Daily Chlorhexidine Bath for Health Care Associated Infection Prevention (CLEAN-IT) trial is a cluster randomized crossover trial to evaluate the use of daily chlorhexidine bathing in critically ill patients in reducing device-associated HCAIs (CLABSI, catheter-associated urinary tract infection [CAUTI], and VAP) compared with soap and water bathing.

## METHODS

The Standard Protocol Items: Recommendations for Interventional Trials (SPIRIT) guidelines were followed for this report.^(
27
)^ The final trial report will follow the Consolidated Standards of Reporting Trials (CONSORT) statement and its extension to cluster randomized trials.^(
28
)^ The trial was registered with ClinicalTrials.gov (NCT05485051) before the inclusion of the first patient.

### Design

The CLEAN-IT trial is an investigator-initiated, multicenter, open-label, cluster-randomized crossover clinical trial assessing the effectiveness of daily chlorhexidine baths in reducing the incidence of device-associated HCAIs in critically ill patients compared with soap and water baths.

The study was conducted in 23 Brazilian intensive care units (ICUs) and is nested in the IMPACTO-MR platform,^(
29
)^ a research platform that collects prospective observational data from more than 50 Brazilian ICUs.

Each participating ICU is a cluster that was randomized to perform the interventions (CHG bathing or soap and water bathing) with crossover for a period of 3 to 6 months, depending on the time of each center’s entrance to the study, with a 1-month washout period between CHG bathing and soap and water bathing transitions.
Figure 1
shows all possible allocation sequences for the participating ICUs.

**Figure 1 f01:**
[figure not shown]
Schematic of possible allocation sequences.

### Study population and interventions

All adult patients ≥ 18 years of age admitted to the participating ICUs were included in the study. Patients were excluded if they were known to have CHG allergies.

### Chlorhexidine digluconate bath

All patients in the ICU during the CHG bath period who did not meet the exclusion criteria were bathed daily with 2% chlorhexidine digluconate (2% CHG). All participating centers received 2% CHG and gloves (soft polyester gloves specifically for hospital bathing) for all CHG bath periods.

The bathing procedure consisted of applying 2% CHG (any form of dilution of the 2% CHG solution was not allowed) with the provided gloves and using it to bathe the patient, ensuring that all the applicable bathing surfaces were covered with 2% CHG and that there were no areas with visible soiling on the patient. The applicable bathing surfaces included all the body surfaces except the eyes, inner ear, mouth, and areas with loss of skin continuity (e.g., open wounds and burnt regions). Bathing was performed in the craniocaudal direction (head to toe), with the last area bathed being the genital region, which was mandatorily washed with a new pair of gloves. Patients were rinsed according to the usual practices of each center.

In cases of extensive soiling, cleaning of the soiled area could be performed before 2% CHG bathing. Other bath-related aspects (e.g., time of day, number of staff involved in each bath, and bedside or shower bath) and infection control practices and bundles followed each center’s usual practices.

### Soap and water bath

All patients in the ICU during the soap and water bath period and washout periods were bathed daily following each center’s usual practices. Chlorhexidine for bathing at any concentration was forbidden during these periods. The only exception was preoperatory bathing for surgical patients, which was allowed in centers with this practice. Other bath-related aspects (e.g., time of day, number of staff involved in each bath, and bedside or shower bath) and infection control practices and bundles followed each center’s usual practices.

### Washout period

The washout period was defined as 1 month between distinct intervention periods (CHG bath period and soap and water bath period). During this period, all centers used soap and water for bathing.

### Randomization, allocation concealment, and blinding

Randomization was performed through cluster randomization with crossover, where the unit of randomization was the ICU. Randomization lists were generated by an independent statistician using R software.^(
30
)^ Randomization was performed by the coordinating center using a central online randomization system (RedCap^®^) on the day of each center’s activation. The intervention sequence was disclosed to the investigators only after all the center’s information was recorded in the online system.

This study is an open-label trial in which patients and investigators are not blinded to the study interventions. The visual aspect and smell of the 2% CHG solution prevents the blinding of patients and study personnel.

### Study outcomes

The primary outcome is the incidence of device-associated HCAIs (CLABSI, VAP, and CAUTI) during the ICU stay within each intervention period. The diagnosis of device-associated HCAIs is made according to the
*Agência Nacional de Vigilância Sanitária*
(ANVISA) definitions.^(
31
)^

The secondary outcomes are the incidence of each specific HCAI (CLABSI, VAP, and CAUTI) within each intervention period, rates of positive microbiological cultures for multidrug-resistant (MDR) pathogens within each intervention period, antibiotic use (measured by days of therapy [DOT] or defined daily dose [DDD]) within each intervention period, ICU and hospital length of stay up to 90 days, and ICU and hospital mortality up to 90 days.

Detailed information on the outcomes and study definitions is available in the
Supplementary Material
.

### Data collection, data sources, and monitoring

Unidentified patient data are routinely collected for the IMPACTO-MR platform by all ICUs and include data on demographics, baseline characteristics, admission diagnosis, severity score (Simplified Acute Physiology Score [SAPS] 3), ICU and hospital length of stay, and mortality. Additional data on HCAIs are collected through a digital online case report form developed by the HCor data management team using REDCap^®^.^(
32
,
33
)^ Additionally, data on antibiotic use during the ICU stay and the results of microbiological cultures collected during the ICU stay are collected from all participating centers using prescription, pharmacy, and microbiology laboratory records.

Access to all data platforms is password protected and supported by the HCor data management team. Data monitoring is performed by the HCor data management team. All data on HCAIs will be monitored, either
*in loco*
or online.

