### Statistical analysis

The main analysis will follow the intention-to-treat framework with patient-level data. Each patient will be analyzed according to the group (CHG or soap and water bath) assigned to the ICU at admission, irrespective of the length of stay and the number of days the patient received each intervention. Patients whose stay crosses into another treatment period will be analyzed according to their initial assignment, and patients admitted during the washout period will not be included in the intention-to-treat analysis. We will perform a sensitivity analysis including only patients admitted and discharged during the same intervention period.

The primary outcome of HCAI incidence per 1,000 patient-days will be analyzed using a Poisson generalized mixed linear model with allocation group, study period, and the interaction of allocation group and study period as fixed effects and center as a random effect. Other possible distributions and models might be considered according to the variable’s behavior. We will use the same model to evaluate the incidence per 1000 patient-days of each specific HCAI (CLABSI, VAP, and CAUTI), rates of positive microbiological cultures for multidrug-resistant pathogens, and antibiotic use. Mortality will be assessed using survival and logistic regression models, taking the center, allocation group, and study period as random effects and the interaction of the allocation group and study period as a fixed effect. Generalized mixed linear models with appropriate distributions will be utilized for other outcomes. Preplanned subgroup analyses will be conducted according to the following characteristics: surgical
*versus*
nonsurgical admission, SAPS 3 score ≤ 40
*versus*
> 40, public
*versus*
private ICU, and ICU length of stay ≤ 7
*versus*
> 7 days.

No adjustments for multiplicity will be performed, and a 2-sided p value of less than 0.05 will be considered statistically significant. All the statistical analyses will be performed using R software (R Foundation for Statistical Computing, Vienna, Austria; https://www.R-project.org/).^(
30
)^

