## DISCUSSION

The CLEAN-IT trial is the first multicenter, randomized clinical trial evaluating the effect of daily bathing with CHG to reduce HCAIs in critically ill patients in an LMIC; it is also expected to be the largest trial in the literature on the subject.

When designing the CLEAN-IT trial, the steering committee faced important issues that should be discussed. One of the distinct aspects of the study is that we chose to use a 2% CHG solution instead of CHG-impregnated bathing cloths. In Brazil and other LMICs, the financial costs of CHG-impregnated bathing cloths would jeopardize the implementation of the intervention if it proves to be effective on a large scale. Therefore, our aim with this protocol was to evaluate a cheaper and readily available intervention with high external validity.

Additionally, we chose to use patient-days as the denominator for the reporting of HCAI incidence instead of device-days given the simplicity and accuracy of patient-day data collection and the equivalence of both metrics and their use in similar studies.^(
1
,
22
,
35
)^

Another design issue is the rationale for performing a cluster randomized trial instead of an individual randomized trial. Bathing practices in intensive care units are usually interventions decided at the unit level and not at the individual level, allowing more uniform delivery of the intervention, due to both the type of intervention and logistical convenience and acceptability. Furthermore, an intervention like the one being studied could have spillover effects on the microbiology of the intensive care unit that could hamper the identification of the effects of the intervention.

Additionally, given restrictions on the study’s budget provided by the Brazilian Ministry of Health after December 31, 2023, we could not wait for all sites to be approved to initiate the study; therefore, the trial started once each center was approved. Coupled with an initial estimate of 50 centers, this staggered inclusion might lead to transitory imbalances in the recruitment rate of each group. However, we will address this in the analysis by considering the time period of each intervention. This time constraint on the trial also led to the choice of a one-month washout period. While more extended washout periods would be ideal to avoid cross-contamination of ICU-level microbiological effects of the intervention, the trial would be unable to be conducted within the planned time frame.

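### The mortality and primary HCAI models contain no patient-level covariate, although SAPS 3 and admission type are already at hand

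*Protocol article*

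**What the plan says.** Under Data collection, data sources, and monitoring, the article states that "Unidentified patient data are routinely collected for the IMPACTO-MR platform by all ICUs". The list includes demographics, admission diagnosis and a "severity score (Simplified Acute Physiology Score [SAPS] 3").

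Under Statistical analysis, "The primary outcome of HCAI incidence per 1,000 patient-days will be analyzed using a Poisson generalized mixed linear model". The terms listed for it are "allocation group, study period, and the interaction of allocation group and study period as fixed effects and center as a random effect". For the individual infections, "We will use the same model to evaluate the incidence per 1000 patient-days of each specific HCAI"; multidrug-resistant cultures and antibiotic use are treated likewise. Mortality is to be assessed by survival and logistic regression, "taking the center, allocation group, and study period as random effects and the interaction of the allocation group and study period as a fixed effect". SAPS 3 and admission type appear in that section only in the subgroup list ("nonsurgical admission, SAPS 3 score ≤ 40" against higher scores, and surgical against nonsurgical).

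On timing, the Discussion explains that centres started as each was approved, and that "this staggered inclusion might lead to transitory imbalances in the recruitment rate of each group". It says the analysis will deal with this by taking account of the time period of each intervention.

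**The concern.** The unit of randomization is the ICU, there are only 21 to 23 of them, and the patients in an ICU's chlorhexidine period are different people from those in its soap period. If the later period happens to receive sicker patients, or fewer surgical ones, the difference goes straight into the treatment comparison as noise or chance imbalance. A severity score bears directly on ICU and hospital mortality, both of them secondary outcomes. The sponsor already treats severity and admission type as relevant enough to define subgroups. Leaving them out of the models gives up precision on mortality. It also leaves the HCAI comparison, in an open-label trial, without a prespecified answer to the question of whether case mix explains the result.

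**Working it through.** The plan gives no figure on this point, so there is none to reproduce. Mortality, AUC, length of stay and size of case-mix shift below are assumptions.

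**1. Model terms side by side**

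| Outcome | Fixed | Random | Patient covariate |
|---|---|---|---|
| Primary HCAI rate | group, period, group × period | centre | none |
| Each HCAI, resistant cultures, antibiotic use | same | same | none |
| Mortality | group × period | centre, group, period | none |
| Length of stay | not stated | not stated | not stated |

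The interaction is group by period. No listed term is centre by period, so nothing absorbs a shift in case mix between two periods of the same ICU.

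**2. Mortality, patient level**

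Assume a logit-normal risk with SD 1.0, 1.3 or 1.6 and mortality of 29% to 32%. This gives AUC 0.74, 0.79 or 0.83. With R² = var(p) / [p̄(1 − p̄)] and equivalent gain in patients = 1/(1 − R²) − 1:

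- AUC 0.74: R² = 0.155; 1/0.845 − 1 = 18%
- AUC 0.79: R² = 0.229; 1/0.771 − 1 = 30%
- AUC 0.83: R² = 0.299; 1/0.701 − 1 = 43%

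These figures are for independent patients, without ICUs or periods.

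**3. Mortality, in a design like this one**

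Take 21 ICUs of 600 patients (the article's sample size) in two equal periods, so 300 per ICU-period, with AUC 0.79 and mortality 0.32. Let s be the SD of mean severity between ICU-periods, beyond sampling chance.

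- Unadjusted variance of an ICU-period proportion: 0.32 × 0.68 / 300 = 0.2176 / 300 = 0.000725, plus (b·s)².
- Slope per SD of severity: b = 1.3 × 0.2176 × 0.771 = 0.218.
- Adjusted variance: 0.000725 × 0.771 = 0.000559.

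Ratio of unadjusted to adjusted variance:

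- s = 0: 0.000725 / 0.000559 = 1.3
- s = 0.1: (0.000725 + 0.000475) / 0.000559 = 2.1
- s = 0.2: (0.000725 + 0.00190) / 0.000559 = 4.7

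A simulation of this design (400 runs, linear model with centre effects) gave about 1.2, 2.2 and 3.9. The last value agrees only roughly. The case s = 0 already contains pure sampling chance (1/√300 = 0.058 SD per ICU-period); larger ratios need a real drift in case mix.

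**4. Primary HCAI rate**

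*Patient-level variation only.* With μ expected events per patient, rate variance σ² and explained share R², the variance removed is R²σ²μ/(1 + σ²μ). At 6 per 1,000 patient-days and an assumed stay of 7 or 10 days, μ = 0.042 or 0.06.

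- Lowest (7 days, σ² = 0.5, R² = 0.1): 0.1 × 0.021 / 1.021 = 0.2%
- Highest (10 days, σ² = 2, R² = 0.5): 0.5 × 0.12 / 1.12 = 5.4%

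Power for a relative risk of 0.91 moves by at most about one point. In simulation the model standard error of the log rate ratio did not change: 0.0890 and 0.0890 with a rate ratio of 1.2 per SD of severity, 0.0905 and 0.0905 with 1.5.

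*With a case-mix shift.* At an assumed 8-day stay, an ICU-period has 0.006 × 8 × 300 = 14.4 events, so Poisson variance is 1/14.4 = 0.0694. Severity contributes (ln RR)² × (s² + 1/300).

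- RR 1.2 per SD, s = 0: 0.0332 / 300 = 0.0001, or 0.2% of the total
- RR 1.5 per SD, s = 0.2: 0.1644 × 0.0433 = 0.0071; 0.0071 / (0.0694 + 0.0071) = 9%

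**5. Calendar time**

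Study period is not defined. Centres started on different dates, with periods of 3 to 6 months depending on entry. If the term means calendar time, the Discussion's promise is met. If it means each ICU's own order, period 1 falls on different dates in different ICUs, and the term cannot carry a calendar trend.

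**The case against.** A crossover analysis without patient covariates is legitimate, since the sequence is randomized and each ICU is meant to supply both arms. Covariate sets and the coding of time are often left to an analysis plan or supplement, and neither is shown. That stands as a reason to rate the point low. It does not dispose of it, because the article writes out the terms of the HCAI and mortality models and severity is not among them.

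The patient-level mortality gains come from simulated independent patients, and part of the severity variance lies between ICUs, where the centre effect already absorbs it. That is fair, and it is why the crossover calculation is given as well. Both rest on assumed inputs.

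A reader might also infer more than the text allows:

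- *That calendar time is ignored.* Study period is a fixed effect in the primary model and the Discussion says time will be considered. The term is undefined, which is not the same as absent.
- *That adjustment would buy useful power for the primary outcome.* For a rare count it buys almost none.
- *That SAPS 3 exists for every patient.* The article says routine collection by all ICUs and gives no completeness.
- *That no analysis of any outcome adjusts for severity.* The terms of the length-of-stay models are not stated.

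Replacing the primary model after inclusion has ended in an open-label trial would also be hard to defend, so the adjusted HCAI model belongs in a supporting role.

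**Conclusion.** The point holds in limited form, as an inexpensive improvement. The written-out mortality and primary HCAI models omit patient-level variables that the trial already collects and already uses for subgroups, and the design does not remove case-mix differences between an ICU's own periods.

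For mortality, SAPS 3 would explain about 16% to 30% of patient-level variance. In the assumed 21-ICU crossover, the unadjusted variance is about 1.2 to 1.3 times the adjusted with no shift beyond sampling chance, and about twice with a 0.1 SD shift. For the HCAI rate the gain is roughly 0% to 9% of variance, and the benefit is protection against a case-mix explanation. All of this depends on assumed mortality, discrimination, stay and shift, none of which the article gives. The calendar-time point is secondary and conditional on what study period means.

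**What to change.** Before database lock:

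1. Add SAPS 3 (continuous) and surgical versus nonsurgical admission as fixed effects in the ICU and hospital mortality models.
2. Report the same adjustment as a supporting analysis of the primary HCAI model, leaving the primary model as it is.
3. Keep and report the unadjusted results throughout.
4. Define study period. If it is within-ICU order, add a sensitivity analysis with a calendar-time term. With 21 to 23 staggered ICUs such a term will overlap with period, so it should be kept simple.

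The cost is wording, since no new data are needed. A rule for missing SAPS 3 values has to be written, and the mortality odds ratio becomes conditional rather than marginal, which the report should say. The article's Perspective section puts the end of inclusion at 31 December 2023 and expected database closure in late March. If closure has passed, the adjusted analyses should be labelled as not prespecified.
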